## Data processing and analysis

The Statistical Package for the Social Sciences (SPSS) version 26.0 will be used to conduct a statistical analysis. The demographic data of the intervention and control groups will be compared at baseline, using appropriate tests (i.e., Mann–Whitney U, *t*-tests, or chi-square). Depending on the normality of the data, an independent *t*-test or a Mann–Whitney *U* test will be used to determine the group differences in both primary and secondary outcomes in T2. Intention-to-treat will be employed as the primary analysis in this study. Potential covariates, such as the duration of caregiving, the number of caregiving hours per week, and the number of referrals will be examined. Within-group differences will be analyzed using either the Wilcoxon signed-rank test (non-parametric) or a paired t-test (parametric). A significant result is indicated when the *p*-value (level of significance) is less than 0.05 for a two-tailed test.

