### Participants and recruitment strategy and randomization

A trained community center staff member will help to generate a list of potential subjects from their membership list. Potential subjects will be called and recruited into the program if they fulfill the following inclusion criteria: (1) aged ≥18 years old, (2) have no cognitive impairment as evidenced by a score of 22 or above in the Hong Kong version of the Montreal Cognitive Assessment (18), (3) can understand and communicate in Cantonese, (4) provide care to older adults aged ≥60 at least 4 h per week for a minimum of 3 months, (5) use a smartphone, (6) know how to access the Internet, (7) commit to attending bi-weekly, 15–30 min online meetings with the program providers over the 3-month period, and (8) are willing to receive individual-specific video messages covering caregiving skills via WhatsApp. They will be excluded if they are (1) known to have serious alcohol and drug problems, (2) are unable to write and read, (3) have mental health problems, and (4) have already participated in other telecare health or social programs. When two or more potential subjects are taking care of the same older adult, only the one who has spent more time with the older adults is allowed to participate.

A trained research assistant (RA) will introduce the program and invite eligible subjects to join the program in the community centers, and obtain verbal consent upon their agreement. After collecting their baseline data, the research assistant will call the principal investigator (PI) of the research team for randomization. The PI will put the numbers generated from a software program called “Research Randomizer” into sealed envelopes (i.e., “1” = intervention group, “2” = control group). These envelopes will be opened sequentially when a call is received from the RA. In this study, the RA and the community center staff will be blinded, but the PI and the healthcare providers will not.

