### Background demographic data

The background demographic data of the participants will be collected at baseline (T1). The data will include age, gender, marital status, level of education, number of caregiving hours per week, work status, duration of caregiving, financial situation, family structure, person with whom they live, and experience of using a smartphone. See Figure 3.

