### Sample size

The sample size will be calculated based on a power analysis. Assuming a two-tailed alpha of 0.05, a probability of 0.2 for the beta error (80% power), and an effect size of 0.403 after referring to a recent telephone-based mHealth program with the same primary outcome measure (perceived stress level) (27), 34 people per group will be required. With reference to the 10–15% attrition rate reported in the previous program (28), we assume a 15% drop-out rate in this study. Thus, the total sample size required is 80 participants (i.e., 40 subjects per group).

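### Baseline significance tests between randomised arms tell the reader nothing, and the unadjusted T2 comparison with an open covariate list gives up available precision

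*Protocol article*

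**What the plan says.** Under Data processing and analysis, the protocol article states that "The demographic data of the intervention and control groups will be compared at baseline, using appropriate tests", and names Mann–Whitney U, t-tests or chi-square as those tests. For the outcomes, an independent t-test or a Mann–Whitney U test "will be used to determine the group differences in both primary and secondary outcomes in T2". No covariate enters either test. A separate sentence adds: "Potential covariates, such as the duration of caregiving, the number of caregiving hours per week, and the number of referrals will be examined". It names no model and no rule for inclusion. The same paragraph sets one general threshold, a p-value that "level of significance) is less than 0.05 for a two-tailed test".

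Background demographic data lists what is recorded at T1: "The data will include age, gender, marital status, level of education, number of caregiving hours per week, work status, duration of caregiving", followed by financial situation, family structure, living companion and smartphone experience, 11 variables in all. On timing, Participants and recruitment strategy and randomization says: "After collecting their baseline data, the research assistant will call the principal investigator (PI) of the research team for randomization".

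**The concern.** Baseline is measured first and individuals are then randomised. If the randomisation is carried out as described, the null hypothesis of each baseline test is true by construction. A small p-value then reports a chance event, and a large one does not show that the arms are balanced on what matters. What matters for the stress comparison is the size of an imbalance multiplied by how strongly the variable predicts T2 stress. A baseline p-value does not measure that product.

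The outcome comparison is fixed as unadjusted, although T1 stress, caregiving hours and duration of caregiving will all be in hand. A chance imbalance in a prognostic variable therefore passes straight into the estimate, and the variance those variables explain stays in the error term. The covariate sentence does not repair this. Its list is open, it does not say how a covariate would enter a t-test or Mann–Whitney U test, and one of its three examples is not a baseline variable. Under Intervention group, referrals are made by the nurse case manager during the programme, so their number is a consequence of allocation. Adjusting for it would remove part of the effect under study.

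**Working it through.** **Inputs from the article.** 11 demographic variables (Background demographic data). 40 randomised and 34 evaluable per arm, effect size 0.403, two-sided alpha 0.05 (Sample size). **Assumption.** The article gives no correlation between any baseline variable and T2 stress, so a range is shown.

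**The plan's own figures.** The drop-out step reproduces: 34/0.85 = 40. The 34 itself does not follow from 0.403 read as a standardised mean difference. The two-sample t-test needs about 98 per arm for 80% power, and 34 per arm gives about 37% (40 per arm, 43%). The article does not state the type of effect size. That is a separate matter, and it is noted here only because it explains why the unadjusted power below is near 37% and not 80%.

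**1. Chance of a false baseline difference.** 1 − 0.95^11 = 0.431, with 11 × 0.05 = 0.55 expected. This treats the variables as independent. Several overlap (marital status, family structure, living companion), so 43% is approximate.

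**2. Imbalance that stays non-significant.** For a continuous variable at 40 per arm, the largest is t(0.975, 78) × √(2/40) = 1.991 × 0.2236 = 0.445 SD. An observed 0.3 SD gives t = 0.3/0.2236 = 1.34, p = 0.18. The chance that a given variable is out of balance by more than 0.2 SD yet non-significant is about 32%; for more than 0.3 SD it is about 13%.

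**3. Effect on the T2 estimate.** Shift = imbalance × r.

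| r (assumed) | Shift at 0.3 SD | Share of 0.403 | Shift at 0.445 SD | Share of 0.403 |
|---|---|---|---|---|
| 0.3 | 0.090 | 22% | 0.134 | 33% |
| 0.5 | 0.150 | 37% | 0.223 | 55% |
| 0.7 | 0.210 | 52% | 0.312 | 77% |

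These are shifts in a single trial that happens to have such an imbalance. Averaged over randomisations they are zero.

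**4. Power from prespecified adjustment.** Simulated at 34 per arm, effect 0.403, two independent covariates each correlated r with T2 stress:

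| r (assumed) | Unadjusted | Two fixed covariates |
|---|---|---|
| 0.1 | about 37% | about 37% |
| 0.2 | about 37% | about 39% |
| 0.35 | about 37% | about 46% |

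One stronger covariate, as T1 stress might be, at 40 per arm: from about 44% to 54% at r=0.5, and from about 43% to 70% at r=0.7.

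**5. Adjusting only when the baseline p<0.05.** Simulated at 40 per arm with one covariate, type I error is 4.3% at r=0.5 and 3.5% at r=0.7, with power about 44% in both cases. With 11 covariates at 34 per arm, two of them at r=0.35, type I error is 4.3% and power about 36%, against about 38% unadjusted in the same simulation. Such a rule would be slightly conservative and would gain nothing.

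**The case against.** The strongest case on the other side has four parts.

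First, a reader might infer that the baseline tests are there to choose the covariates, so that adjustment follows chance p-values. The article does not say so. The two sentences are not linked, and duration of caregiving and caregiving hours are named without any condition on a baseline test. This part stands, and the point here does not rely on that link.

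Second, a reader might infer that the 5% error rate is broken. It is not. The unadjusted randomised comparison keeps its level over repeated randomisations, and adjusting after a baseline pre-test falls slightly below it (step 5). Taking the smallest p-value of five adjusted and unadjusted versions would give about 8.6%, but nothing in the article describes that practice. This part also stands.

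Third, a covariate set is often left to an analysis plan, and this is a condensed article. That is fair as far as a missing rule goes. It does not cover what the article fixes: significance tests of baseline demographics, an unadjusted T2 comparison, and a post-randomisation variable named as a covariate.

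Fourth, the precision gain rests on assumed correlations. This stands in part. For caregiving hours and duration the gain could be close to nothing, since the article does not document their prognostic value. That is a reason to include T1 stress, the same scale measured earlier, and not to rely on the two demographic variables alone.

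**Conclusion.** The point holds as one of analysis choice and efficiency, and it merits a change. The baseline p-values carry no usable information, with about a 43% chance of at least one false difference if the 11 variables are independent. Imbalances of up to 0.445 SD would pass as non-significant at 40 per arm. At assumed correlations of 0.3 to 0.7, an imbalance of that size would move the stress estimate by 33% to 77% of the planned effect, and the planned test leaves it uncorrected. The power forgone runs from nothing (two covariates at r=0.1) to about 9 points (two at r=0.35), and more if T1 stress is strongly correlated with T2 stress. These power figures read 0.403 as a standardised mean difference. The documents support neither a claim of inflated type I error nor a claim that covariates are selected by baseline tests.

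**What to change.** Replace the baseline sentence with: *Baseline characteristics, including T1 PSS and the other T1 scales, will be summarised by arm; no significance tests of baseline differences will be done.*

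Replace the covariate sentence with: *The between-group model for T2 PSS will include T1 PSS, caregiving hours per week and duration of caregiving, all measured at T1, as fixed covariates whatever their observed balance. No covariate will be added or dropped on the basis of a baseline test or of T2 results. The unadjusted comparison will be reported alongside.*

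Remove number of referrals from the covariates. It can be described within the intervention arm as a measure of programme delivery.

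The cost is three degrees of freedom out of 66 at 34 per arm, and the loss of baseline p-values that some readers expect in the first table. No extra data or participants are needed. This does change the primary between-group analysis from unadjusted to adjusted, so it should be recorded as an amendment and dated before T2 data are compared by arm. The article does not show whether that stage has been reached.

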### Data collection

Data will be collected at two time points – pre-intervention (T1) and post-intervention (T2). The data will be collected through phone call by a trained RA. Five percent of completed questionnaires (i.e., 4) will be randomly selected for an independent review to ensure the quality of the collected data.

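### The between-group comparison uses T2 scores only, by a test chosen from the data; a pre-specified ANCOVA on the baseline score would be more precise and would fix the effect measure

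*Protocol article*

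**What the plan says.** All references are to the Protocol article.

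- **Between-group test** (Data processing and analysis). Two tests are offered, the unpaired t-test and its rank-based counterpart (Mann-Whitney), and the one picked according to how normal the scores look "will be used to determine the group differences in both primary and secondary outcomes in T2". No normality check or threshold is named.
- **Measurements.** "Data will be collected at two time points", T1 and T2 (Data collection). The section on participants, recruitment and randomization places baseline collection before the call for allocation, so every randomised participant should have a T1 score on the PSS-14, the primary outcome.
- **Use of T1 outcome scores** (Data processing and analysis). They appear only in paired t-tests or Wilcoxon signed-rank tests within each arm.
- **Covariates** (same section). Potential covariates are to be examined. The examples are caregiving duration, weekly caregiving hours and number of referrals. Baseline PSS-14 is not named, and no adjusted model is described.
- **Sample size.** "Assuming a two-tailed alpha of 0.05", 80% power and "an effect size of 0.403 after referring to a recent telephone-based mHealth program", the article concludes that "34 people per group will be required", raised to 40 per group for 15% drop-out.

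**The concern.** The score most likely to predict T2 stress is T1 stress on the same scale. The trial collects it from everyone and then leaves it out of the only comparison that contrasts the arms. In a trial of 80 people this gives away precision and leaves the result open to chance baseline imbalance.

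Two further features add to this. The normality rule lets the data decide whether the primary result is a difference in PSS points or a rank comparison, so the effect measure is not fixed beforehand. The within-group tests share the general 0.05 threshold although they do not compare the arms, and nothing says that conclusions rest on the between-group contrast.

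The covariate sentence does not close the gap. One of its examples, number of referrals, arises after randomisation: the Intervention group section describes referrals as made by the nurse case manager during the programme. Adjusting for it could remove part of the treatment effect.

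**Working it through.** **Inputs from the article (Sample size).** Two-sided alpha 0.05; power 80%; effect size 0.403, whose type is not stated and which is read here as a standardised mean difference d; 34 evaluable per group; 40 per group randomised.

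**Input not in the article.** The T1-T2 correlation r of PSS-14. Assumed values are 0.3, 0.5 and 0.7.

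**Step 1: the plan's own figure.** For a two-sample t-test at d = 0.403, alpha 0.05 and 80% power, the exact noncentral-t solution is 97.6, so 98 per group and not 34. If 0.403 were Cohen's f (d = 2 × 0.403 = 0.806), 80% power would need 26 per group; 34 per group then corresponds to 90% power, which is not what is stated. The drop-out step does reproduce: 34/0.85 = 40.

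**Step 2: T2-only power at 34 per group.** Noncentrality = d × √(n/2) = 0.403 × √17 = 1.66, with 66 degrees of freedom and critical t 1.997. Power is 37%.

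**Step 3: ANCOVA on T1.** The variance of the contrast is multiplied by (1 − r²), so the effective d is 0.403/√(1 − r²). The lost degree of freedom is ignored here and taken up in Step 4.

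| r | Variance factor | Equivalent gain in participants, 1/(1 − r²) − 1 | Effective d | Power at 34 per group | n per group for 80% power | Detectable d at 34 per group, 80% power |
|---|---|---|---|---|---|---|
| T2 only | 1.00 | none | 0.403 | 37% | 98 | 0.69 |
| 0.3 | 0.91 | 10% | 0.422 | 40% | 89 | 0.66 |
| 0.5 | 0.75 | 33% | 0.465 | 47% | 74 | 0.60 |
| 0.7 | 0.51 | 96% | 0.564 | 63% | 51 | 0.49 |

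The last column does not depend on what kind of effect size 0.403 is.

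**Step 4: statistical cost of ANCOVA.** Critical t moves from 1.9966 to 1.9971. Estimating the slope inflates the variance by about 1 + 1/64 = 1.016. ANCOVA therefore gains once r² exceeds 1 − 1/1.016, that is, once r exceeds about 0.12.

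**Step 5: chance imbalance.** With 40 per group, the baseline difference between arms has standard deviation √(2/40) = 0.22 SD units, and about 32% of trials start at least that far apart. An imbalance of 0.22 shifts the expected T2 contrast by r × 0.22, which is 0.07, 0.11 or 0.16 SD at r = 0.3, 0.5 or 0.7. This is the same loss of precision seen another way, not an additional one.

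**Step 6: the normality rule.** This was simulated with 34 per group, underlying r = 0.5 and 5,000 runs per scenario, using Shapiro-Wilk at 0.05 as an assumed check.

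| Data | Planned rule (t or Mann-Whitney) | t-test | ANCOVA |
|---|---|---|---|
| Normal, power at 0.403 | 37% | 37% | 46% |
| Lognormal, power at 0.403 | 59% | 40% | 48% |

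With no effect, rejection rates were 4% to 6% for every test.

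**The case against.** **The planned test is not wrong.** Comparing T2 scores between randomised arms is unbiased and valid. A reader might infer that the normality rule inflates false positives; the simulation shows no material inflation. What remains is that the effect measure is left to the data and precision is lost.

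**The covariate list is open.** Its examples are introduced as examples, so baseline PSS-14 is not excluded, and an unseen analysis plan may name it. A reader might infer that baseline data are thrown away altogether. That is too strong, because T1 scores are used within arms and adjustment is at least foreshadowed. But the article does commit to a between-group test, that test is on T2 scores, and nothing commits to baseline adjustment.

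**The gain rests on an unstated correlation.** This stands. At r = 0.3 the gain is only from 37% to 40%.

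**ANCOVA is not always the more powerful choice.** This also stands. With strongly skewed scores the planned rule reached 59% power against 48% for ANCOVA, although Mann-Whitney tests a different quantity. It is a reason to add a rank-based sensitivity analysis.

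**The within-group tests need not mislead anyone.** A separate between-group test is planned. A reader might infer that a significant change in the intervention arm alone would mislead in some definite share of trials. The documents support no such figure: it depends on r and on the improvement common to both arms, and neither is given.

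**Conclusion.** The point holds as a choice that is valid but avoidably weak. The stated between-group analysis does not use the baseline score, and the effect measure is not fixed in advance. For assumed r of 0.3, 0.5 or 0.7, the variance given up is 9%, 25% or 49%. Reading 0.403 as a standardised mean difference, power at 34 per group would rise from 37% to about 40%, 47% or 63%. These gains are against the T2 t-test with roughly normal scores.

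A reader might infer that ANCOVA rescues the sample size. It does not: reaching 80% power at d = 0.403 with 34 per group requires 1 − r² = 34/97.6, so r of about 0.81. That 34 per group does not follow from 0.403 at 80% power is a separate problem and should be dealt with separately. The change recommended here should be made, but the planned comparison would not be invalid without it.

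**What to change.** 1. Pre-specify ANCOVA of T2 PSS-14 on arm and T1 PSS-14 as the single primary analysis. Report the adjusted mean difference with a 95% confidence interval, using a robust or bootstrap interval if residuals are skewed.
2. Replace the normality-driven choice of test with a stated rank-based sensitivity analysis.
3. Use the same model for each secondary scale, with its own baseline.
4. Keep number of referrals out of the adjustment set. Adjustment for centre is optional, since the article describes no stratification by centre.
5. State that conclusions rest on the between-group contrast, and show within-group changes descriptively.

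This is a change of wording, with no new data and no extra participants. The statistical cost is one degree of freedom and possibly less power than a rank test if scores turn out strongly skewed.

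### Intention-to-treat is declared primary, but the named T2 test uses observed cases only unless something is added; a T1/T2 mixed model would serve the declaration better

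*Protocol article*

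**What the plan says.** All of this is in the protocol article.

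- **Analysis principle** (Data processing and analysis): "Intention-to-treat will be employed as the primary analysis in this study".
- **Between-group test** (same section): an independent t-test or a Mann–Whitney U test, chosen on normality, "will be used to determine the group differences in both primary and secondary outcomes in T2". The within-group tests are paired, so they need a T2 score too.
- **Covariates** (same section): duration of caregiving, "the number of caregiving hours per week, and the number of referrals will be examined". No adjusted model is named, and the baseline stress score is not among the examples.
- **Assessments** (Data collection): T1 and T2 only, by telephone, by the research assistant. Each participant therefore has one post-baseline score. The section on recruitment and randomisation places baseline collection before the envelope is opened, so a T1 score should exist for everyone randomised.
- **Expected loss** (Sample size): 34 per group are required and "we assume a 15% drop-out rate in this study", which gives 40 per group and 80 in total. The section cites 10–15% attrition from an earlier programme.

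The article does not say how a participant without a T2 score enters the intention-to-treat analysis. It does not say whether people who leave the programme are still phoned at T2. It also nowhere restricts the analysis to completers.

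**The concern.** The principle covers everyone randomised, whereas the test can be computed only on those with a T2 value. Nothing in the article joins the two for participants whom the sponsor expects to lose. If the analyst runs the named test on the data as they stand, the result will be an observed-case comparison reported under an intention-to-treat label.

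That comparison is unbiased only if, within each arm, having a T2 score is unrelated to what the score would have been, or if the resulting distortions cancel between arms. Neither can be taken for granted here. The arms ask for different effort: the intervention involves bi-weekly Zoom meetings, weekly videos and a website, while the control arm receives usual services with optional attendance. The outcome is perceived stress, which may itself affect who stays. Both remarks are inferences about what could happen; the article documents neither.

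The second loss is of information. The T1 PSS-14 score is collected on everyone and is the obvious predictor of the T2 score, yet the named comparison leaves it out.

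**Working it through.** **Inputs.** From the Sample size section: 34 per group, 15% assumed drop-out, 10–15% cited range, 40 per group, planning effect 0.403. The 34 is taken as given; whether it follows from 0.403 is a separate question. The shifts of 0.5 and 1.0 SD and the T1–T2 correlations below are assumptions and come from nowhere in the article.

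**1. The plan's own figure.** 34 / (1 − 0.15) = 40 per group, and 2 × 40 = 80. This reproduces exactly.

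**2. Participants outside the named test, if every drop-out also misses the T2 call.**

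- At 15%: 80 × 0.15 = 12 without T2, 80 − 12 = 68 with T2 (34 per group).
- At 10%: 80 × 0.10 = 8 without T2, 80 − 8 = 72 with T2.

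If some drop-outs still answer the call, the numbers without T2 are smaller; if all do, they are zero.

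**3. Illustrative bias in a difference of means.** Let p be the share of an arm without T2, and δ the amount, in SD, by which those people would have scored above the observed members of the same arm (a higher PSS-14 score is worse). The observed mean is then too low by p × δ. With benefit defined as control minus intervention,

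observed benefit = true benefit + (p × δ in the intervention arm) − (p × δ in the control arm).

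With informative loss in one arm only:

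| p | δ = 0.5 SD | δ = 1.0 SD |
|---|---|---|
| 0.10 | 0.10 × 0.5 = 0.05 | 0.10 × 1.0 = 0.10 |
| 0.15 | 0.15 × 0.5 = 0.075 | 0.15 × 1.0 = 0.15 |

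The benefit is overstated if the worse-scoring drop-outs are in the intervention arm, and understated by the same amount if they are in the control arm. Equal p × δ in both arms cancels.

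**4. Scale against the planning effect.** If 0.403 is a standardised mean difference, the range is 0.05 / 0.403 = 12.4% to 0.15 / 0.403 = 37.2%. The article does not state the metric. If 0.403 is Cohen's f, the standardised difference is 2 × 0.403 = 0.806, and the range is 0.05 / 0.806 = 6.2% to 0.15 / 0.806 = 18.6%.

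**5. What using T1 would add.** Adjusting for a baseline score with T1–T2 correlation ρ multiplies the residual variance by 1 − ρ²: 0.91 at ρ = 0.3, 0.75 at ρ = 0.5 and 0.51 at ρ = 0.7. It also weakens the missing-data assumption. Missingness may then depend on arm and on T1 stress, and the estimate stays valid as long as it does not further depend on the unseen T2 score.

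**The case against.** The strongest reply is that this is an omission in a condensed article. Intention-to-treat says who is analysed and in which arm; a t-test says how the arms are compared. A t-test on imputed T2 scores, or on scores collected after someone leaves the programme, is consistent with the declaration. The missing-data rule may sit in a full protocol or analysis plan that is not shown.

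Much of this stands. A reader might infer from the test and the 15% allowance that the plan delivers a completer analysis, or that the test and the declaration contradict each other. The document supports neither reading. Dividing 34 by 0.85 is routine protection of power and is equally used in trials that impute. T2 is collected by the research assistant by phone, separately from the nurse's Zoom sessions, so leaving the programme need not mean a missing score. The bias figures rest on assumed shifts and can run either way; that drop-out will favour the intervention is conjecture.

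What does not fall is the choice of test. The article is not silent on the analysis: it names the principle, the software, the tests and the significance level. A bare request for a missing-data rule would be a request for detail. The point here is that the comparison it does name leaves out a baseline score already collected and needs a stronger missing-data assumption than an alternative available at almost no cost.

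**Conclusion.** The point holds in a limited form. As named, the between-group test reduces to observed T2 cases unless something is added, and it makes no use of T1 PSS-14. Up to 12 of 80 randomised participants would not contribute at the plan's own drop-out rate (8 at the lower end of the cited range), on the assumption that all drop-outs also miss the T2 call. The possible bias is of unknown size and sign; 0.05 to 0.15 SD is an illustration for loss in one arm, not a prediction. The article is incomplete on this point, not self-contradictory, and nothing in it shows an intention to analyse completers. The case for change rests on a better primary analysis being readily available.

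**What to change.** - **Primary analysis.** Replace the T2-only test with a linear mixed model that has T1 and T2 PSS-14 as responses, a common mean for both arms at T1 (justified because T1 precedes randomisation), separate arm means at T2 and an unstructured covariance. The treatment effect is the arm difference at T2. Include all 80 participants in the arm assigned. SPSS, the software already named, can fit this. An acceptable alternative is multiple imputation of T2 using T1, followed by a T1-adjusted comparison.
- **T2 follow-up.** State that the T2 phone call is made to everyone randomised, including those who stop attending Zoom sessions. This does more than any model, because it reduces the number of missing scores.
- **Supportive analysis.** Keep the t-test or Mann–Whitney U test on observed T2 scores, labelled as an observed-case analysis.
- **Optional.** A delta-adjusted sensitivity analysis, with shifts applied in either arm, would show how far the result depends on the missing-data assumption.

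The cost is slightly more analysis work. The T2 calls are already the method of data collection. The main downside is that the model relies on missing-at-random given T1 and arm, which cannot be verified, and with only one post-baseline score T1 is the main source of information about those without T2. The change should be fixed before outcome data are seen.
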